## Abstract

**Background:**

Stroke is a leading cause of disability and distress, and often profoundly affects the quality of life of stroke survivors and their carers. With the support of carers, many stroke survivors are returning to live in the community despite the presence of disability and ongoing challenges. The sudden and catastrophic changes caused by stroke affects the mental, emotional and social health of both stroke survivors and carers. The aim of this study is to evaluate a Stroke and Carer Optimal Health Program (SCOHP) that adopts a person-centred approach and engages collaborative therapy to educate, support and improve the psychosocial health of stroke survivors and their carers.

**Methods:**

This study is a prospective randomised controlled trial. It will include a total of 168 stroke survivors and carers randomly allocated into an intervention group (SCOHP) or a control group (usual care). Participants randomised to the intervention group will receive nine (8 + 1 booster) sessions guided by a structured workbook. The primary outcome measures for stroke survivors and carers will be health-related quality of life (AQoL-6D and EQ-5D) and self-efficacy (GSE). Secondary outcome measures will include: anxiety and depression (HADS); coping (Brief COPE); work and social adjustment (WSAS); carer strain (MCSI); carer satisfaction (CASI); and treatment evaluation (TEI-SF and CEQ). Process evaluation and a health economic cost analysis will also be conducted.

**Discussion:**

We believe that this is an innovative intervention that engages the stroke survivor and carer and will be significant in improving the psychosocial health, increasing independence and reducing treatment-related costs in this vulnerable patient-carer dyad. In addition, we expect that the intervention will assist carers and stroke survivors to negotiate the complexity of health services across the trajectory of care and provide practical skills to improve self-management.

**Trial registration:**

ACTRN12615001046594. Registered on 7 October 2015.

## Background

Stroke is the second leading cause worldwide of death (11 %) and serious long-term disability [1, 2]. The significant burden of stroke extends across individuals, families and health systems globally [2, 3]. For the carer, a sudden shift from an acute hospital stay to informal care is experienced, as a family member or significant other contends with a new role and a dependent loved one [4, 5]. Equally important are the healthcare professionals who administer appropriate medical treatment and fulfil ongoing management and education roles for the stroke survivor across the illness trajectory [6]. However, in an oversubscribed and under-resourced health environment other innovative support methods are warranted. The Stroke and Carer Optimal Health Program (SCOHP) will adopt a person-centred approach combining collaborative therapy and care co-ordination to support and improve the mental and physical health of stroke survivors and their carers.

### Importance of the stroke-survivor-carer dyadic relationship

The strength of the dyadic relationship is crucial for achieving optimal mental and physical health for both the stroke survivor and carer. Alongside the stroke survivor, the carer must adjust to the immediate and long-term effects that require varying degrees of assistance and a consequent reduction in occupational and social activities [4, 7]. The nonprofessional carer role is complex and under-recognised encompassing information provision, managing emotions, social support, health maintenance and problem solving [8, 9]. The new-found role of carer is accompanied by intricacies and interdependencies including potential role reversals and unexpected physical, cognitive and emotional demands [8–11]. In addition, studies continue to report that early hospital discharge combined with a lack of appropriate planning can adversely impact rehabilitation and contribute to carer burden [12, 13]. Subsequently, carers also experience adverse health effects with high rates of depression, anxiety, increased morbidity and mortality [13–15]. This is of great concern given that informal carer involvement in rehabilitation is imperative to recovery.

### Stroke psychosocial interventions

In recent years research into the field of stroke has shifted from a physical emphasis to include psychological elements with a focus on carers; however, the stroke survivor/carer dyad has received minimal attention. Further, the evidence base regarding the effectiveness of support interventions for carers and/or stroke survivors is insufficient and inconsistent, primarily owing to methodological issues such as the diversity of intervention outcome measurements [6, 16, 17].

One of the most robust published studies was a randomised controlled trial of tailored psychoeducational modules and skill-building strategies (e.g. hands-on caregiver training and goal setting) delivered to 300 informal carers of stroke patients over three to five inpatient sessions and one home visit, which improved survivor and caregiver outcomes and reduced costs [18]. However, home visits are not always feasible and the individually tailored topics and goal setting focused more on the care of the stroke survivor than on the carer’s own self-care.

A recent critical analysis of 17 caregiver and 15 caregiver/stroke survivor dyad intervention studies produced evidence-based recommendations for the implementation and future design of stroke informal caregiver and dyad interventions [6]. Based on American Heart Association guidelines for classes and levels of evidence, interventions identified at the highest level of evidence were those that:combine skill-building (e.g. problem solving, stress management, goal setting) with psychoeducational strategiestailor interventions to the needs of stroke caregivers based on needs assessments along the continuum of caredeliver the program face to face and/or by telephone (when in-person contact is not possible)offer an optimal number of sessions, which is between five and nine [6].

Unfortunately, few validated psychosocial interventions specific to carers are available, and for those that are, the mechanisms of effectiveness are rarely described [19]. A recent review evaluating the effectiveness of psychosocial interventions for informal carers found limited evidence regarding the effectiveness of psychosocial interventions, although psychoeducation, consisting of training in problem solving and stress coping, reduced depression and improved carer sense of competency at the trend level [16]. Overall, current limited evidence points towards more rigorous design of multidisciplinary psychosocial interventions, sustainability of outcomes and inclusion of the stroke survivor-carer dyad.

### Translating Research, Integrated Public Health Outcomes and Delivery (TRIPOD)

This randomised controlled trial (RCT) is part of a larger research program – TRIPOD – which will evaluate our Optimal Health Program (OHP) across three chronic conditions; namely stroke, diabetes mellitus and chronic kidney disease, including cost-effectiveness analyses. Based on a collaborative therapy framework [20], the OHP was originally developed to support people with mental illness [21, 22]. The initial trial, in an adult mental health service, demonstrated significant improvements in health and social functioning, reduced hospital admissions and net cost savings per patient [22]. A key aspect of collaborative therapy is recognising that ‘recovery’ and chronic models of health care are not dichotomous [20]. With the intention of enhancing self-efficacy, self-management, care co-ordination and quality of life, the OHP has been adapted within the broader context of chronic disease. Thus, in the current series of trials our OHP is used to implement this therapeutic framework to enable clinicians and consumers to work systematically towards the achievement of optimal psychosocial health outcomes within mainstream health services [23]. The self-management foundations of the OHP are particularly relevant for adults affected by stroke and their carers who face the daily challenge of managing various and often simultaneous aspects of their disease such as managing multiple medications, cognitive training, ongoing appointments, and physiotherapy as well as coping with the emotional impact of stroke and their care regimen. This protocol describes an RCT (SCOHP) that has been designed to evaluate the OHP for those affected by stroke – survivors and carers.

### Qualitative study: informing development of an optimal health program

Healthcare provider experiences of carers have been researched, but little is written about how these can inform development of support programs. In collaboration with the National Stroke Foundation, Carers Victoria and three consumers (one carer and two stroke survivors) a qualitative study was undertaken to inform development of an Optimal Health Program (OHP) to support carers of those who have experienced a stroke [24]. The aims of the qualitative study were to inform SCOHP by: (1) exploring healthcare provider perceptions of stroke carer roles and support needs and (2) examining carer needs across the stroke care trajectory. To achieve this, we conducted four semi-structured focus groups (*n* = 23) of stroke healthcare providers across acute, subacute, and community rehabilitation services. Focus group facilitators used a semi-structured focus group schedule to guide discussions. Sessions were then recorded, transcribed, and analysed using thematic and content analysis. Table 1 shows the three key themes and sub-themes that emerged from the data, which highlight the distinct roles of healthcare providers and carers.

**Table 1 Tab1:** Themes and sub-themes from thematic analysis

Themes	Sub-themes
Transition	Healthcare provider roles across stages of the stroke trajectory
	Carer transition to a caring role and how this changes over time
Information	Delivery of information by healthcare provider
	The carers’ response to information and difficulties comprehending implications
Impact of stroke	Healthcare provider role in supporting the carer and person with stroke and maintaining hope
	Carers’ experiences of the impact of stroke

**Table 2 Tab2:** Primary and secondary outcome assessments and time points for SCOHP

	Carer				Stroke survivor			
Assessment tools	BL	3	6	12	BL	3	6	12
Primary outcomes								
AQoL-6D (20 items)	X	X	X	X	X	X	X	X
GSE (10 items)	X	X	X	X	X	X	X	X
Secondary outcomes								
BIPQ (8 items)					X	X	X	X
Brief COPE (28 items)	X	X	X	X	X	X	X	X
CASI (30 items)	X	X	X	X				
CEQ (6 items)	X				X			
EQ-5D -3 L (6 items)	X	X	X	X	X	X	X	X
HADS (14 items)	X	X	X	X	X	X	X	X
HCUQ (10 items)	X	X	X	X	X	X	X	X
MCSI (13 items)	X	X	X	X				
TEI-SF (9 items)				X				X
BFI-10 (10 items)		X				X		
WSAS (5 items)	X	X	X	X	X	X	X	X

*AQoL*-*6D* Assessment of Quality of Life-6 dimensions, *GSE* General Self-Efficacy Scale, *BIPQ* Brief Illness Perceptions Questionnaire, *Brief COPE* abbreviated version of the COPE Inventory, *CASI* Carers’ Assessment of Satisfaction Index, *CEQ* Credibility/Expectancy Questionnaire, *EQ*-*5D*-*3L* European Quality of Life-5-dimensions-3 levels, *HADS* Hospital Anxiety and Depression Scale, *HCUQ* Health Care Utilisation Questionnaire, *MCSI* Modified Caregiver Strain Index, *TEI*-*SF* Treatment Evaluation Inventory-Short Form, *BFI*-*10* Big Five Inventory-10 item, *WSAS* Work and Social Adjustment Scale

The findings of this study were used to inform the development of the OHP, specifically in terms of having: staged information across the illness trajectory; flexible support during transition periods; and a balance of practical tools and empathic communications around the impact of stroke. In summary, the discussions held with health providers supported the integration of an OHP for carers within existing stroke care services across acute and community settings.

### Research aims

The aim of the study is to determine whether a stroke-specific OHP (SCOHP) improves the psychosocial health of stroke survivors and their carers, compared to usual care. The primary objective is to identify the impact of the OHP on levels of self-efficacy and quality of life for those affected by stroke. Secondary objectives are to evaluate the impact of the SCOHP on depression, anxiety, social and workplace functioning, self-management, and illness perceptions of and coping with stroke, and carer strain and satisfaction.

In addition, a health economic cost analysis will be performed, assuming an Australia-wide implementation, to identify any cost savings of SCOHP over current practice. Quality-adjusted life years (QALYs) will be measured using the Assessment of Quality of Life-6D (AQoL-6D) [25] and European Quality of Life-5 dimensions-3 levels (EQ-5D-3L) [26]. Process evaluation using focus groups will also be conducted with patients and clinicians to assess the effectiveness of the SCOHP, implementation, uptake and service delivery.

## Methods

### General design

This is a prospective randomised controlled trial to evaluate the effectiveness of the SCOHP for improving the psychosocial health of those who have experienced stroke and their carers. The SCOHP will be delivered as an 8-week individualised support program, with an additional booster session, and will be compared to usual care. Assessments will take place at baseline, 3, 6, and 12 months. The study protocol was approved by the St Vincent’s Hospital Human Research Ethics Committee (HREC-A 019/14). An executive steering committee (all authors) oversees project planning, conduct and ongoing data collation.

### Setting

The study will be conducted at the neurology unit of St Vincent’s Hospital, a large metropolitan teaching hospital in Melbourne, Australia. Between 2011 and 2012, 737 patients were admitted to St Vincent’s Hospital, with a principal diagnosis of stroke. The stroke unit at St Vincent’s Hospital, Melbourne will enable planned recruitment of 168 participants for the SCOHP program over a 2-year period.

### Participants

A total of 84 patients diagnosed with stroke, and 84 carers of these patients, will be recruited into the RCT. For the purposes of this study, stroke is defined as cerebral infarction or parenchymal haemorrhage confirmed by medical records. The following criteria are to be met for inclusion into the RCT: (1) diagnosis of stroke for patient or self-nominated carer of a stroke patient; (2) 18 years or older; (3) ability to converse in English without an interpreter or professional assistance; (4) absence of developmental disability or amnestic syndrome impairing their ability to learn from the intervention; and (5) absence of serious comorbid illness, including severe forms of aphasia, as identified by the nurse unit manager, and cognitive impairment, as identified from medical notes scoring lower than 24 on the Mini-Mental State Examination (MMSE) [27]. As the OHP adopts a holistic approach to managing chronic disease, patients may enter the program at any stage along the continuum of care.

Power was calculated to detect a medium effect size of Cohen’s *d* = 0.50. This was chosen as a clinically meaningful effect size that may be compared with previous RCT research in the area of chronic disease management programs [28]. Calculations assumed two primary outcomes (health-related quality of life and General Self-Efficacy Scale (GSE) scores), four assessment points (baseline, 3-month, 6-month, and 12-month), a study-wide type I error rate (α) of .05, and hence a type II error rate (β) of 0.20 (power of 0.80), a correlation of post-treatment scores with baseline measurements (ρ) of 0.81, and a two-tailed statistical test [29]. To detect an effect size of Cohen’s *d* = 0.50, 53 participants in each of the control and intervention groups will be required. Allowing for up to 20 % attrition, a total of 168 participants, or 42 carers and stroke survivors in control and intervention groups will be recruited.

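### The step from 53 required per arm to 168 recruited does not follow from 20 % attrition, and the two figures appear to come from different calculations

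*Protocol article*

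**What the plan says.** The power paragraph is in the protocol article, Methods, Participants. Its inputs are:

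- Effect size: "Power was calculated to detect a medium effect size of Cohen’s *d* = 0.50".
- Outcomes and visits: "Calculations assumed two primary outcomes" (health-related quality of life and GSE) and "four assessment points (baseline, 3-month, 6-month, and 12-month").
- Error rates: "a study-wide type I error rate (α) of .05" and "a type II error rate (β) of 0.20 (power of 0.80"), with a two-tailed test.
- Correlation: "a correlation of post-treatment scores with baseline measurements (ρ) of 0.81".

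The result is that "53 participants in each of the control and intervention groups will be required". After an allowance of up to 20 % for attrition, "a total of 168 participants, or 42 carers and stroke survivors in control and intervention groups will be recruited". The same section splits the 168 into 84 patients and 84 carers, so each arm has 42 survivors and 42 carers, or 84 people.

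The paragraph does not say whether 53 counts both roles together or each role separately, how alpha is divided between the two primary outcomes, or which formula was used. Randomisation and blinding says that patients and carers are randomised as dyads, or singly if they take part alone. Outcome measurements gives both roles the same primary measures. Statistical analyses plans an MMRM of the 3-, 6- and 12-month scores with baseline as covariate, and does not say whether the roles are modelled together or apart.

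**The concern.** The required number, the attrition allowance and the recruitment target stand in consecutive sentences, and the first two should produce the third. They do not, whether 53 is read as pooled or as per role. One of the printed figures is therefore wrong as written, or a step between them is not described.

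The statement of 80 % power rests on these figures. If 53 per arm pooled is right, 168 is more than 20 % attrition calls for. If 53 per arm is needed in each role, the trial is short of its own requirement from the first day. If the true requirement is 67, the printed 53 is wrong and 168 is right. These cases have different consequences for reading a null result, and the paragraph does not let the reader tell them apart.

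**Working it through.** **1. The printed chain.** Inputs: 53 per arm, 20 % attrition, 168 recruited, 42 per arm per role (all from Participants).

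- Pooled roles: 53/(1 − 0.20) = 66.25, rounded up to 67 per arm; 2 × 67 = 134.
- Multiplying instead of dividing: 53 × 1.2 = 63.6, so 64 per arm; 128 in total.
- 53 per arm in each role: 4 × 67 = 268.
- Attrition implied by 168: 1 − 106/168 = 0.369, or 37 %.
- Per role before dropout: 42 < 53. After 20 % loss: 42 × 0.8 = 33.6.
- Inflating twice does reach the target (53/0.8 → 67; 67/0.8 = 83.75 → 84; 2 × 84 = 168), but nothing in the text supports a second inflation.

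**2. Can 53 be reproduced?** For two means, n per arm = 2(z₁₋α/₂ + z₀.₈₀)²/d² × V, where V is the variance factor. With d = 0.50 and V = 1 this is 62.8 at alpha .05 and 76.0 at alpha .025. The .025 is an assumed equal split over the two primary outcomes; the protocol does not state it.

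| Formula, ρ = 0.81 | V | n per arm, α .05 | n per arm, α .025 |
|---|---|---|---|
| Single score, unadjusted | 1 | 63–64 | 77–78 |
| Baseline-adjusted ANCOVA, 1 − ρ² | 0.3439 | 22–23 | 27–28 |
| Change score, 2(1 − ρ) | 0.38 | 24–25 | 29–31 |
| Mean of four assessments, (1 + 3ρ)/4 | 0.8575 | 54–55 | 66–67 |

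Each range runs from the normal approximation to the t-based value. In the last row, 62.8 × 0.8575 = 53.8 and 76.0 × 0.8575 = 65.2. At alpha .05 that row comes within one or two of 53, and power at exactly 53 per arm is 0.79.

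**3. Can 168 be reproduced?** The last row at alpha .025 gives 67 evaluable per arm (t-based). Then 67/0.8 = 83.75 → 84 per arm, and 2 × 84 = 168, with power 0.80. At alpha .05 the same formula gives 55/0.8 = 68.75 → 69 per arm, or 138 in total. So 53 goes with alpha .05 and 168 with alpha .025.

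**4. What 168 delivers** (noncentral t, d = 0.50, ρ = 0.81):

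| Basis | Evaluable per arm | Formula | Power, α .05 | Power, α .025 |
|---|---|---|---|---|
| Pooled, members treated as independent | 67 | four-assessment | 0.87 | 0.80 |
| Per role | 33–34 | four-assessment | 0.58–0.59 | 0.46–0.48 |
| Per role | 33–34 | ANCOVA | 0.93 | 0.88–0.89 |

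**5. Within-dyad correlation.** The document gives no value. Assuming 0.1 to 0.5 and complete pairs, the design effect is 1.1 to 1.5, and 67 becomes 60.9 to 44.7 effective per arm. At alpha .025, Φ(0.5/√0.8575 × √(n/2) − 2.241) gives about 0.77 to 0.62.

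**The case against.** The strongest reply is that both numbers have a plausible source. The paragraph lists four assessment points among its inputs, and the usual repeated-measures formula with those inputs comes close to 53 and reaches 168. A reader might infer from the broken chain that the figures reproduce on no reading and that the 80 % power has no valid derivation. The document does not support that: the pooled, four-assessment reading at alpha .025 gives 168 with power 0.80. What remains is that this reading needs 67 where the text prints 53, and the alpha that yields 53 does not yield 168.

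A second reply is that some other allowance may bridge the gap. A design effect of 134.4/106 = 1.27, that is a within-dyad correlation of about 0.27, would carry 53 per arm to 168 with 20 % attrition. The paragraph names attrition alone, so this is conjecture, but only the sponsor can rule it out.

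Three further inferences are tempting and should be resisted.

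- That 53 is really a two-arm total, because ANCOVA at alpha .025 gives 26.15 per arm and 2 × 26.15 = 52.3. Rounded up per arm, the total is 54 or 56, and the text says each group.
- That power falls steadily as ρ falls. That holds for ANCOVA. Under the four-assessment formula it reverses: with 33.6 per arm at alpha .05, power is 0.59 at ρ = 0.81 and 0.72 at ρ = 0.50.
- That every primary comparison will rest on about 34 completers per arm. Statistical analyses does not say that the roles are analysed separately, and the MMRM uses all available data.

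One point cuts the other way. The four-assessment formula averages baseline into the outcome, whereas the planned MMRM uses baseline as a covariate, and ρ is described as a correlation with baseline. Approximating 53 and 168 does not show that the formula suits the planned analysis.

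**Conclusion.** The point holds as an inconsistency between printed figures. With 20 % attrition, 53 per arm leads to 134 (pooled) or 268 (per role), not 168, and 42 per arm per role is below 53. This part is plain arithmetic and needs no assumption.

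That 53 and 168 come from different calculations is an inference. It rests on the four-assessment formula and on an alpha of .025 per outcome, which the protocol does not state.

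The trial is not shown to be underpowered. Pooled, 168 gives about 0.80 to 0.87 before any allowance for dyads. Per role, it gives 0.88 to 0.93 under ANCOVA with ρ = 0.81, but only 0.46 to 0.59 under the formula that approximates 53. The stated power cannot be confirmed until the basis is named.

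**What to change.** Keep 168 as the recruitment target and make the paragraph consistent with it.

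1. Have the sponsor confirm the original calculation. If alpha .025 per primary outcome was used, replace 53 by 67 evaluable per arm, pooled, so that one inflation for 20 % attrition gives 84 per arm and 168. If 53 is confirmed, restate the total that 20 % attrition implies, or name the further allowance that takes it to 168.
2. State the alpha per outcome, the formula, how ρ enters it, and whether the requirement is pooled or per role. If pooled, say how within-dyad correlation is handled.
3. Restate the power that 168 delivers on that basis.

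Do not insert 27–28 per arm unless the sponsor confirms an ANCOVA basis. That figure comes from a formula that does not yield 53.

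The cost is a few sentences and a small power table, with no extra participants as long as 168 stands. The drawback is that the stated power becomes conditional and may be less favourable than the 80 % now printed.
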